#### Maternal and foetal anthropometry and body composition

##### Maternal

Height will be measured only at the baseline measurement with a stadiometer (Seca 22, Hamburg). Pre-pregnancy weight will be based on self-report. Height measurement and pre-pregnancy weight will be used to calculate BMI (weight[Kg]/height[m2]) [65].

One month after delivery (postpartum period) lean, fat and bone mass of the whole body will be measured using a dual-energy x-ray absorptiometry (DXA) device (Hologic Discovery QDR, Nasdaq: HOLX). Waist circumference (cm) will be assessed at the middle point between the ribs and the ileac crest, with the participant standing (Harpenden anthropometric tape, Holtain Ltd).

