## Methods/design

### Study design

A supervised RCT (registration number: NCT02582567) based on an exercise program will be conducted in 60 overweight (body mass index (BMI) ≥ 25–29.9), or grade I obese (BMI ≥ 30–34.9) pregnant women (*n* = 30 in the exercise intervention group vs. 30 controls) from Granada (southeaster Spain). The organizational and participants flow is presented in Fig. 1.

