1st day evaluation						
Sociodemographic data		X				
Clinical history		X		X	X	X
Weight and height	X	X		X		X
Body composition (dual-energy x-ray absorptiometry)						X
Accelerometry		X	X	X		
Physical fitness		X		X		
Nutritional study		X		X		X
Questionnaires to be fill there or at home between the 1st and 2nd evaluation days						
Low back-pain		X		X		X
Quality of life		X		X		X
Sleep quality		X	X	X		X
Physical activity		X	X	X		X
Self-perceived physical fitness		X	X	X		X
Sexual function		X		X		X
Restless legs syndrome		X		X		X
Mental and positive health		X		X		X
2nd day evaluation: Accelerometers collection and review of questionnaires		X		X		
Maternal biochemical analysis		X		X	X	
Umbilical cord blood sampling					X	
Maternal urine sampling		X		X	X	

Blood samples (5 mL) of all pregnant participants will be extracted at week 16th and 34th of gestation, and at delivery. Samples of venous and arterial blood from the umbilical cord (5 + 5 mL) at the time of delivery will be taken. In addition, samples of urine at 16 and 34 weeks gestation and delivery will be collected. All samples will be immediately frozen and conserved at −80 °C to avoid breaking the cold chain before being sent to the laboratory.

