## Statistical analysis

Since this study aims at determining potential biological effects of exercise, the statistical analysis will be performed on a per-protocol basis, thus, including in the analyses only participants who attended at least 80 % the exercise session and completed both baseline and follow-up evaluations. The treatment effects will be reported as between-group changes on the primary and secondary outcomes and will be assessed with generalized linear models after adjusting for baseline values. All the analyses will be repeated additionally adjusting for age and any other confounder potentially not well balanced at baseline, and the results from both models will be reported. The effect size (95 % confidence interval) and statistical significance will be reported for each study outcome. The statistical significance will be set at α = 0.05. Sensitivity analyses will be conducted using intention-to-treat analyses and baseline observation carried forward imputation.

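### DXA body composition has no baseline scan, so the stated baseline-adjusted change analysis cannot be applied to it; naming baseline weight and height as covariates would recover precision at no cost in data

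*Protocol article*

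**What the plan says.** The Abstract lists body composition among the secondary outcomes. The Maternal part of the anthropometry section fixes the time of the scan: "One month after delivery (postpartum period) lean, fat and bone mass of the whole body will be measured". Table 2 agrees, with a single mark for DXA in the last column (1 month post-partum) and none at weeks 12, 16, 24 or 34 or at delivery.

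The Statistical analysis section sets one rule for every outcome. On the estimand: "The treatment effects will be reported as between-group changes on the primary and secondary outcomes". On the model, effects "will be assessed with generalized linear models after adjusting for baseline values". A second model is then run, "additionally adjusting for age and any other confounder potentially not well balanced at baseline", and both sets of results are reported. The main analysis set is per-protocol, with an 80% attendance threshold.

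Measures of starting size are available. The Table 2 row "Weight and height" is marked at weeks 12 and 16, and randomisation follows the baseline evaluations. The Maternal section adds: "Height measurement and pre-pregnancy weight will be used to calculate BMI", the pre-pregnancy weight being self-reported. None of these is named as a covariate for DXA.

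**The concern.** The analysis rule and the measurement schedule do not fit together for this outcome. With one scan per woman there is no DXA change to report and no DXA baseline to put in the model. Taken as written, the main model for fat, lean and bone mass then contains the group term and nothing else.

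This matters because the women are recruited over a wide range of size, "overweight (body mass index (BMI) ≥ 25–29.9), or grade I obese (BMI ≥ 30–34.9) pregnant women", and allocation is by simple randomisation with no stratification on BMI or weight stated. Much of the woman-to-woman spread in post-partum body mass is likely to reflect size before the intervention. A model that ignores it leaves that spread in the residual and widens the confidence interval.

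The second model does not close the gap. It admits weight or BMI only if someone judges the arms unbalanced after seeing the data. A strongly prognostic covariate earns its place through its correlation with the outcome, whether or not the arms happen to differ on it.

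**Working it through.** **Schedule against rule (all from the protocol article)**

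- DXA times: 1 month post-partum only (Table 2; Maternal section).
- Change from baseline: cannot be formed, as there is one measurement.
- Baseline value of the outcome: does not exist.
- Main model for DXA: group only.
- Second model: age, plus other covariates chosen on observed imbalance.
- Pre-randomisation size measures: weight at weeks 12 and 16, height, and BMI.

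**The plan's own calculation.** The only sample-size calculation is for weight change: difference 1.04 kg, SD 1.15 kg, power 90%, α 0.05. Taken as two-sided,

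n per group = 2 × (1.15/1.04)² × (1.960 + 1.282)² = 25.7, so 26.

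This reproduces the stated 26 per group. It says nothing about DXA: the 1.15 kg is the SD of a change within women, not of a single post-partum mass.

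**Illustration of the precision at stake.** The protocol gives no SD, expected effect or correlation for DXA, so the following are assumptions: a fat-mass difference of 2 kg, a between-woman SD of 5 kg, and a correlation r of 0.5 to 0.8 between the baseline covariate and post-partum fat mass. The 26 women per arm is the protocol's number before its allowance for withdrawals.

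- Residual SD = 5 × √(1 − r²)
- Standard error of the arm difference = residual SD × √(2/26)
- Power from the noncentral t distribution, 50 degrees of freedom, two-sided α 0.05, noncentrality = 2 / standard error

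| r | Residual SD (kg) | Standard error (kg) | Noncentrality | Power |
|---|---|---|---|---|
| 0 (unadjusted) | 5.00 | 1.39 | 1.44 | 29% |
| 0.5 | 4.33 | 1.20 | 1.67 | 37% |
| 0.7 | 3.57 | 0.99 | 2.02 | 51% |
| 0.8 | 3.00 | 0.83 | 2.40 | 65% |

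The gain is 8 to 36 percentage points. Residual variance falls to 75%, 51% or 36% of its unadjusted value. That is the precision of an unadjusted comparison with about 35, 51 or 72 women per arm (26/0.75, 26/0.51, 26/0.36). Giving up one or two degrees of freedom (50 to 49 or 48) changes these powers by less than 0.1 percentage point.

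**A smaller effect.** With a 1 kg difference and the same SD, power is 11% unadjusted and 13%, 17% or 22% at r = 0.5, 0.7 or 0.8. Adjustment helps, but DXA remains underpowered.

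**The case against.** The strongest reply is that the Statistical analysis section is a general statement covering about a dozen outcome families. Birth weight, Apgar score, type of delivery and the cord glucose/insulin ratio have no baseline either, so the natural reading is to adjust for baseline where one exists. Covariates for one secondary outcome may also sit in an analysis plan that is not shown. This has force: the sentence is loose rather than perverse, and nothing states that DXA must go without covariates. What remains is that the article does fix a rule for secondary outcomes, and the rule cannot work here. DXA also differs from the delivery outcomes in having close stand-ins, weight and height, taken in every woman before randomisation.

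A second reply is that the repeat analysis would catch a visible imbalance in weight or BMI. That is partly right, and both results are to be published. But the choice is then made on the data, and the precision is lost in the main model whenever the arms look balanced.

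A reader might go further and infer that an unadjusted DXA comparison would mainly show which arm started heavier, or that chance differences in starting weight would drown the effect. The documents do not support that. Under randomisation such imbalance is already in the standard error: the estimate is unbiased on average and the type I error rate holds. Nor is the 1.04 kg from the Sample size section a fair yardstick, since it is a difference in weight change and not a DXA effect.

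Bias can enter by another route. Attendance at exercise sessions can remove women only from the exercise arm. If attendance depends on starting size, the per-protocol arms will differ in it systematically. Adjusting for weight and height would reduce that part, but not selection on other grounds. The intention-to-treat sensitivity analysis helps only partly, because its baseline carried-forward imputation has no DXA baseline to carry.

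**Conclusion.** The point stands as a mismatch between rule and schedule for one secondary outcome. As written, the main DXA analysis is in effect an unadjusted post-partum comparison, described as a change that cannot be calculated. The main consequence is lost precision, with some added exposure to selection on starting size through the per-protocol set.

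The size is conditional. The 8 to 36 point gain in power rests on an effect, an SD and correlations that the protocol does not give, and it is worked for fat mass only; lean and bone mass may correlate differently with starting size. Adjustment would not make DXA a well-powered outcome for small effects. The change is worth making because it costs almost nothing, not because the trial's main conclusion depends on it.

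**What to change.** Add a sentence to the Statistical analysis section for the DXA outcomes (fat, lean and bone mass). The main model includes measured week-16 weight and height (or BMI) as covariates named in advance, for every woman and whatever the observed imbalance. Measured week-16 weight with height is preferable to BMI built on self-reported pre-pregnancy weight. State also that these results are reported as adjusted between-group differences one month post-partum, not as changes.

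The cost is one or two degrees of freedom per model. No extra scan, visit or data item is needed.

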##### Foetus/newborn

A monitoring of the evolution of the foetal anthropometrics will be performed by obstetrical ultrasound measurements following the standards of the International Society of Ultrasound in Obstetrics and Gynaecology guidelines and the methodology by Perin et al. [66]. The baby also will have a physical examination within 24 h after birth. Baby’s weight, length and head circumference will be measured. Newborns will be classified as having low birth weight or macrosomia when birth weight was less than 2500 g and greater than 4000 g, respectively.

#### Dietary patterns

The *Mediterranean Diet Score* [67] in a version adapted to the specific needs during pregnancy for Fe, Ca and folic acid [68] will be used to assess the adherence to the traditional Mediterranean dietary pattern. A moderate alcohol diet, also typical of the Mediterranean Diet, will not be considered for calculating the index in this group of women, who should not drink alcohol due to their pregnancy.

The *frequency of consumption* of foods will be also studied by means of a quantitative questionnaire, validated and designed by Mataix et al. [69].

#### Physical fitness

Participants’ physical fitness status in the 16th and 34th week of pregnancy will be assessed by means of the following tests:

##### Cardiorespiratory fitness

Aerobic capacity will be estimated with a submaximal cycle ergometer heart rate method. A pedaling rate of 50 rpm will kept constant by use of a metronome. Initial workload, 50 W or 75 W, will be based on the women’s reported physical activity levels, and increased by 25 W per minute until a steady state heart rate of 125 · beats or more · per minute was reached, after which the women will cycle for at least 6 min until two consecutive heart rates, one minute apart, differ by 3 or fewer beats · per minute. The VO_2max_ will be calculated according to the Åstrand and Ryhming nomogram [70].

We will additionally perform the *6*-*min walk* test, which measures the maximum distance (in meters) each participant can walk in 6 min along a 45.7 m rectangular course [71].

##### Upper-body muscle strength

The *handgrip strength* will be measured using a digital dynamometer (TKK 5101 Grip-D; Takey, Tokyo, Japan) as described elsewhere [72]. The participants will perform (alternately with both hands) these tests twice. The best value of 2 trials for each hand will be chosen and the average of both hands will be used in the analyses.

##### Upper-body flexibility

The *back*-*scratch* test, a measure of overall shoulder range of motion, involves measuring the distance between (or overlap of) the middle fingers behind the back with a ruler [71]. The best score of two attempts for each arm in centimetres will be recorded and the average of both arms will be used in the analyses.

##### Self-perceived physical fitness

The *International Fitness Scale* [73] is composed of five Likert-scale questions asking about the perceived participants’ overall fitness, cardio-respiratory fitness, muscular fitness, speed-agility and flexibility in comparison with their friends’ physical fitness (“very poor”, “poor”, “average”, “good” and “very good”).

#### Low-back pain

Pregnant women usually report low-back pain, especially in the third gestational trimester. Low-back pain will be assessed with the Spanish version of the *Oswestry Disability Index score* [74]. We will additionally employ the Pain Visual Analogue Scale to assess low back pain intensity [75].

#### Physical activity and sedentary behaviour

*Accelerometry* will be used to objectively assess PA and sedentary time. Women will be asked to wear a tri-axial accelerometer (ActiSleep+, Pensacola, Florida, United States) for 9 consecutive days, starting the same day they receive the monitor (e.g. participants who receive the accelerometer on Monday, will carry the device until Tuesday of the next week). The first and last day will be excluded from the analyses, accounting for a total of 7 days of registering. Participants will be instructed to wear the accelerometer during the whole day (24 h) on their wrist attached by an elastic belt. To prevent any damage to the devices, these will be taken off during water-based activities such as bathing or swimming. Time engaged in light, moderate, and moderate-vigorous intensity PA and sedentary time will be calculated. This accelerometer has been previously used in pregnancy with similar methodology as described in the present protocol [19].

#### Haematology and biochemical analysis

Venous blood samples will be extracted in standardized fasting conditions at 8–9 a.m. in the hospital and collected in EDTA vacuum tubes, and tubes for serum. Some samples will be centrifuged at 1750 rpm for 10 min at 4 °C in a refrigerated centrifuge (GS-6R Beckman, Fullerton, CA, USA) to separate plasma from formed elements. Subsequently, erythrocytes will be centrifuged in a hypertonic solution to remove membranes and cytosol.

##### Haematology

Erythrocyte count, haematocrit, haemoglobin, platelets, leukocytes and erythrocyte mean corpuscular volume will be quantified by a Coulter counter.

##### Biochemical parameters

Plasma total, high-density lipoprotein and low-density lipoprotein cholesterol, triglycerides, phospholipids, creatine kinase, aspartate aminotransferase, alanine aminotransferase, gamma-glutamyl transferase, lactate dehydrogenase, alkaline phosphatase, glucose, urea, insulin, albumin, high sensitivity C-reactive protein, glycosylated haemoglobin, creatinine, total bilirubin, myoglobin, lactate, troponin I, peroxisome proliferator-activated receptor-γ coactivator (PGC)-1α, nitric oxide and myeloperoxidase will be assessed with standard methods using an autoanalyzer (Hitachi-Roche p800, F. Hoffmann-La Roche Ltd. Switzerland) or by using commercial kits (spectrophotometry and ELISA).

#### Oxidative stress

##### a) Antioxidant defence

Plasma measurements: liposoluble antioxidants (vitamin E, retinol, carotene, coenzyme Q10 and coenzyme Q9) through mass spectrometry and the total plasma antioxidant capacity by using commercial kit (spectrophotometry).Erythrocyte measurements: liposoluble antioxidants in membrane (vitamin E and coenzyme Q10) through mass spectrometry and antioxidant enzymes activity (catalase, glutathione peroxidase and superoxide dismutase) by spectrophotometry.

##### b) Oxidative damage

Oxidative damage to proteins: measurement of carbonyl proteins by using commercial kit (spectrophotometry).Oxidative damage to lipids: measurement of 4-hydroxynonenal and isoprostanes in urine and plasma and hydroperoxides in plasma and erythrocyte membrane by using commercial kits (spectrophotometry and ELISA).Oxidative damage to DNA: measurement of 8-hydroxyguanosine in urine and plasma by commercial kits (ELISA).

#### Pro- and anti-inflammatory signal

Some maternal and umbilical cord plasma pro-inflammatory and anti-inflammatory cytokines (IL-1β, IL-2, IL-6, IL-8, IL-10, IFN-γ and TNF-α, IL-1ra and TNF Srii α), some adipokines (adiponectin, adipsin, resistin, PAI-active, insulin and leptin) and myokines (irisin) will be measured by the employment of Luminex xMAP technology.

#### Bone biomarkers

Various relevant biomarkers related to bone metabolism (ACTH, DKK-1, FGF-23, Osteocalcin, OPN-Osteopontin, Osteoprotegerin, PTH and SOST) will be measured with Luminex xMAP technology.

#### Sleep quality

The *Pittsburgh Sleep Quality Index* [76] will be used to assess sleep quality and disturbances over a l-month time interval. Nineteen individual items generate seven “component” scores: subjective sleep quality, sleep latency, sleep duration, habitual sleep efficiency, sleep disturbances, use of sleeping medication, and daytime dysfunction. Each component yields a score ranging from 0 to 3, with 3 indicating the greatest dysfunction. The seven component scores are summed to provide a global sleep quality score (range 0 to 21) with higher scores indicating poor sleep quality.

Nevertheless, it has been shown that reported sleep by pregnant women varies in relation to that objectively estimated with accelerometry [77]. Consequently, behaviours related to sleep, such as sleep onset, sleep latency, total sleep time, number and duration of awakenings and sleep efficiency will be objectively calculated by using a triaxial accelerometer (ActiSleep+, Pensacola, Florida, United States). The data analysis of such ActiSleep accelerometry data will be carried out through its specific software (Actilife).

#### Quality of life, mental health and positive health

We will use the *Short*-*Form Health Survey 36* [78], for assessing health-related quality of life. It contains 36 items grouped into 8 dimensions: physical functioning, physical role, body pain, general health, vitality, social functioning, emotional role, and mental health. The scores range from 0 to 100 in every dimension, where higher scores indicate better health.

The pregnant antenatal depression will be assessed with the *Center for Epidemiological Studies*-*Depression Scale* questionnaire [79], which is validated and widely employed in pregnancy. Postnatal depression levels will be assessed with the Spanish version of the *Edinburgh Postnatal Depression Scale* [80], which is a 10-items self-report scale designed as a specific instrument to detect postnatal depression.

Anxiety levels will be assessed with the *State Trait Anxiety Index* [81]. This questionnaire consists of two scales that assess anxiety state and trait anxiety. The total score ranges from 20 to 80, with higher values indicating higher levels of anxiety.

The “Restless Legs Syndrome” largely determines the quality of life for many pregnant and is related to their levels of depression and sleep quality [82]. The Spanish version of the *Detention of Restless Legs Syndrome* questionnaire [83] will be employed to assess the presence and severity of this syndrome.

Sexual function is also an important aspect of the quality of life of a person. The Spanish version of the *6*-*item Female Sexual Function Index* [84] was used to assess sex function. This instrument is composed of six questions: desire, arousal, lubrication, orgasm, satisfaction and pain. Each question can be scored from 0 to 5 and then summed up to provide a total score.

Finally, “positive health” will be evaluated through the following questionnaires:The *Trait Meta-Mood Scale* [85] is comprised of 3 subscales to assess participant’s beliefs about attending to and value their feelings (emotional attention), feel clear rather than confused about their feelings (emotional clarity) and how well participants regulate their moods and repair negative emotional experiences (emotional repair). Each subscale comprises 8 items. Participants rate their responses using a 5-point Likert type scale, with 1 = “strongly disagree” to 5 = “strongly agree”. The subscales score range from 8 to 40 and higher scores reflect greater attention, clarity, and repair.The *Positive and Negative Affect Schedule* [86] is a 20-item questionnaire designed to measure positive and negative affect. The questionnaire includes 10 positive and 10 negative emotional states that should be answered on a 5-point Likert scale, from 1 = “very slightly or not at all” to 5 = “extremely”. The score ranges from 10 to 50 for both subscales (positive affect and negative affect), and higher scores reflect greater affective well-being.The *10*-*item Connor-Davidson Resilience Scale* [87, 88] assesses resilience to stress, which is a construct refers to a dynamic process of positive adaptation to adverse changes in life circumstances. Each item ranges from 0 = “not true at all” to 4 = “true nearly all the time”. The total score range from 0 to 40, and higher scores indicate greater resilience.

## Statistical analysis

Since this study aims at determining potential biological effects of exercise, the statistical analysis will be performed on a per-protocol basis, thus, including in the analyses only participants who attended at least 80 % the exercise session and completed both baseline and follow-up evaluations. The treatment effects will be reported as between-group changes on the primary and secondary outcomes and will be assessed with generalized linear models after adjusting for baseline values. All the analyses will be repeated additionally adjusting for age and any other confounder potentially not well balanced at baseline, and the results from both models will be reported. The effect size (95 % confidence interval) and statistical significance will be reported for each study outcome. The statistical significance will be set at α = 0.05. Sensitivity analyses will be conducted using intention-to-treat analyses and baseline observation carried forward imputation.

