## Exercise intervention

Most of exercise programs developed for pregnant women until now [20, 27, 52] have been designed in compliance with the recommendations of the American College of Obstetrics and Gynaecology (ACOG) in 2002 [53], or the Canadian Society for Exercise Physiology, among others [54]. However, in 2011, Zavorsky & Longo [55] launched a more actual, specific, and evidence-based guideline for exercise programs during pregnancy. Consequently, the exercise program that will be conducted in the present project has been developed accordingly to this guideline [55]. Nonetheless, we have also followed similar studies [56, 57] where aerobic and resistance training, as well as strengthening of the pelvic floor muscles [58], have been developed successfully and in line with these recommendations [57].

The exercise intervention (*n* = 30) will be performed in three groups of 10 participants and will meet the training standards of the American College of Sports Medicine [59] for adults. The groups will train 3 days/week (55–60 minutes per session) from the 17th week of gestation until delivery. The exercise sessions will be designed, carefully supervised, guided and instructed by qualified exercise professionals with experience in working with pregnant women.

The exercise program planning is shown in Table 3. The exercise intervention group will have different phases: a) *Information phase*: which will involve the understanding of the intervention plan for them, the goals we want to work with them, and how we will perform it (one training session); b) *Movement Learning phase*: theoretical and practical sessions with the explanation of movements and explanation of basic movement patterns (two training sessions); and c) *Physical Fitness Training phase*: with training sessions aimed at improving fitness and weight management (from the 18th until the 34th gestational week), and training sessions focused on a correct pelvic mobilization for the delivery (after the 34th gestational week until delivery) in order to try to reduce caesarean section rate, delivery time and number of pushes [23, 60].

**Table 3 Tab3:** Supervised exercise intervention program

SESION STRUCTURE	CONTENT										
WARM-UP 10 min	Joint mobility and different walk modalities										
CONDITIONING 40 min	Training week	1	2–4	5–6	7–8	9–10	11–12	13–14	15–16	17–18	>19
	Gestational week	17	18–20	21–22	23–24	25–26	27–28	29–30	31–32	33–34	>34

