## Primary and secondary outcomes

### Primary outcome

The primary outcomes are maternal weight gain and maternal and foetal glycaemic profile. Maternal weight gain will be defined as the weight change from baseline measurement to the last measurement at 34th week of gestation. Maternal insulin sensitivity will be derived from the homeostatic model assessment for insulin resistance (HOMA-IR), which will be calculated using the formula [fasting insulin (μIU/mL) × fasting glucose (mg/dL)]/405 in the 34th week of gestation. Neonatal insulin sensitivity will be assessed through the cord blood ratio glucose/insulin.

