Not less important for an optimal pregnancy is a healthy psychological status [31, 32, 96]. In that sense, exercise represent an excellent opportunity to improve quality of life [33] and reduce cortisol levels, which may in turn have a positively influence on the foetus and child [31, 32]. Besides, it is unknown whether exercise could positively influence the characteristic worse sleep quality during gestation [48, 49], which can alter the pregnant metabolic status [41–43] and gestational outcomes [44–46] and negatively affect the pregnant quality of life [37–40] and the foetal development [47].

There is a clear and compelling rationale for increased pregnancy research in order to address the therapeutic needs of pregnant women [93]. Additionally, there is accumulating evidence that pregnancy provides a unique window into understanding fundamental mechanisms underlying observed links between a pregnant woman’s health and her later health and the health of her children [93]. The information obtained from this RCT will therefore be of clinical and public health interest and will suggest future research. Further, the exercise intervention designed is novel and non-expensive, and can be easily transferred to other similar contexts. Consequently, the findings of the GESTAFIT Project will help the Health Systems to identify strategies for primary prevention and health promotion among overweight and obese pregnant.

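### The main analysis is per-protocol, with an 80% attendance rule that can exclude women from the exercise arm only and has no stated time window; intention-to-treat should be primary

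*Protocol article*

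**What the plan says.** The Statistical analysis section gives its reason first: "Since this study aims at determining potential biological effects of exercise". It then states that "the statistical analysis will be performed on a per-protocol basis, thus, including in the analyses only participants who attended at least" 80% of the exercise sessions and who "completed both baseline and follow-up evaluations". Treatment effects come from generalized linear models adjusted for baseline values, and a second model adds age and any imbalanced confounder. Intention-to-treat appears only among the sensitivity analyses, named alongside baseline observation carried forward.

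Four other places bear on this:

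- **Exercise intervention.** The exercise arm has three supervised sessions a week "from the 17th week of gestation until delivery". Training for fitness and weight management ends at week 34, and later sessions are pelvic mobilisation for delivery. Controls receive general advice, three seminars and brochures, and no supervised sessions.
- **Primary outcome.** Maternal weight gain is the "weight change from baseline measurement to the last measurement at 34th week of gestation". HOMA-IR is also taken at week 34. The neonatal glucose/insulin ratio comes from cord blood, so at delivery.
- **Table 1.** A note restricts the data analysis by birth outcomes, among them term delivery, appropriate newborn weight, Apgar score and cord pH.
- **Discussion.** The findings "will help the Health Systems to identify strategies for primary prevention and health promotion among overweight and obese pregnant".

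**The concern.** Randomisation makes the two groups comparable as allocated. A rule applied after randomisation that can act on one arm only gives up that protection. Here, women who keep attending an exercise class are set against controls who have passed no equivalent test. Those who attend may differ from those who stop in motivation, in health during pregnancy or in weight trajectory. The controls who would have attended, had they been allocated to exercise, cannot be identified.

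An interest in biological effects does not solve this, because it does not make attenders comparable with controls. Adjustment for baseline values and age cannot be relied on either. Motivation may go unmeasured, and a health change after randomisation can affect both attendance and weight.

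The rule covers every primary and secondary outcome. At stake are the meaning of the headline difference and the 5% error rate attached to it. A second weakness is that the 80% has no stated window, although sessions continue after two of the three primary outcomes have been measured.

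**Working it through.** **1. The plan's own figure.** The inputs, from the Sample size section, are a difference of 1.04 kg, SD 1.15 kg, power 90% and α 0.05 (two-sided assumed). Then n per arm = 2 × (1.960 + 1.282)² × 1.15² / 1.04² ≈ 25.7, so 26 per group, as stated. The noncentral t distribution gives power 0.892 at 26 per group. The allowance from 52 to 60 women is for loss to follow-up only; it does not cover exclusions for attendance. With 26 completers per arm and an assumed 80% of exercisers meeting the rule (21 against 26), power is 0.855. With all 30 per arm observed and the effect undiluted, it is 0.931.

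**2. Who can be excluded.**

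| Criterion | Exercise arm | Control arm |
|---|---|---|
| At least 80% of exercise sessions | can exclude | cannot exclude |
| Both evaluations completed | can exclude | can exclude |
| Birth-outcome criteria (Table 1 note) | can exclude | can exclude |

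Only the attendance rule is one-sided, although all three select after randomisation.

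**3. Possible size of the bias, with no true effect.** The documents give neither the attendance rate nor its correlation with weight gain, so both are assumed. Let propensity to attend be normal, have correlation ρ with weight gain, and let a proportion *a* of exercisers meet the rule. The expected spurious difference is ρ × [φ(z)/a] × SD, where z = Φ⁻¹(1 − a) and φ is the normal density.

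- a = 0.8: φ(z)/a ≈ 0.350. With ρ = -0.2: -0.2 × 0.350 × 1.15 ≈ -0.08 kg, which is 8% of 1.04 kg.
- a = 0.6: φ(z)/a ≈ 0.644. With ρ = -0.5: -0.5 × 0.644 × 1.15 ≈ -0.37 kg, which is 36% of 1.04 kg.

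Type I error was simulated with 20,000 runs, 26 completers per arm and a two-sided t-test at 0.05 without covariates:

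| ρ | 80% adherent | 70% adherent | 60% adherent |
|---|---|---|---|
| -0.2 | -0.08 kg; 5.6% | -0.11 kg; 6.0% | -0.15 kg; 6.3% |
| -0.3 | -0.12 kg; 6.4% | -0.17 kg; 7.2% | -0.22 kg; 8.7% |
| -0.5 | -0.20 kg; 8.8% | -0.29 kg; 12.4% | -0.37 kg; 16.6% |

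With ρ = 0 or a = 1 the rule causes no bias.

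**4. The attendance window.** Weeks 17 to 34 hold 18 × 3 = 54 sessions. If the denominator runs to delivery, a woman who attends all 54 and none later scores:

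| Sessions run through week | 37 | 38 | 39 | 40 | 41 | 42 |
|---|---|---|---|---|---|---|
| Scheduled | 63 | 66 | 69 | 72 | 75 | 78 |
| Attendance | 86% | 82% | 78% | 75% | 72% | 69% |

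The limit is 54/0.8 = 67.5 sessions. She passes at 67 scheduled sessions (54/67 = 81%) and fails at 68 (54/68 = 79%), which falls within week 39. Exposure before the week-34 measurements is the same in every column.

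**The case against.** The plan is open about its choice, gives a reason, and pre-specifies an intention-to-treat analysis, so a randomised comparison will be available. Baseline adjustment and the second model may absorb some of the selection, and the simulation above includes neither. All of this stands, but it does not change which result is the headline.

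Three stronger readings are tempting, and the documents do not support them.

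- **That the rule counts sessions held after week 34.** No window is stated. Counting to delivery is the literal reading, since sessions run to delivery. A denominator ending at week 34 is also plausible for weight, because the programme changes purpose there. A condensed article may leave this detail to a fuller document. The supportable point is that the rule as printed is unclear and that one reading has an undesirable effect. The worked example, full attendance and then none, is also an extreme pattern. For the cord-blood outcome a denominator running to delivery is correctly timed.
- **That the result is biased in favour of exercise and the 5% error rate fails.** Size and direction depend on adherence and on its correlation with outcome, and neither is given. The rate may not hold; the documents do not show that it fails.
- **That selected exercisers are compared with all controls.** Controls must also complete both evaluations, and the Table 1 criteria apply to them too.

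The Discussion sentence about health systems is general and is no analysis commitment. It shows only the use the authors foresee for the result.

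**Conclusion.** The concern holds in this form: the main analysis is per-protocol, its attendance rule can exclude exercise-arm women only, and the headline comparison is therefore not the randomised one and is open to selection bias. That much follows from the text without any assumption.

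The size does rest on assumptions. Over 60–80% adherence and a correlation of 0.2–0.5 between attendance and lower weight gain, the effect ranges from slight (-0.08 kg, type I error 5.6%) to serious (-0.37 kg, 16.6%). The missing window is a secondary point. It concerns weight gain and HOMA-IR and matters only if the denominator runs past week 34. The main defect should be corrected before analysis, because it touches every outcome and the remedy is already half planned.

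**What to change.** - Make intention-to-treat (all randomised women, as allocated) the primary analysis for every outcome, with per-protocol supportive.
- Do not apply the birth-outcome criteria of the Table 1 note to the primary set. They conflict with analysing all randomised women.
- Do not use baseline observation carried forward for weight in pregnancy. It would impute no gain from the week-16 baseline for a woman whose week-34 weight is missing. Use a likelihood-based or multiple-imputation approach.
- In the per-protocol set, state the window for each outcome and count only sessions scheduled before that outcome is measured: weeks 17 to 34 for weight gain and HOMA-IR, and up to delivery for cord blood.
- Optionally, add a complier-average estimate with randomisation as the instrument, to address the biological question. Women below an 80% cut still receive some exercise, which strains its exclusion assumption, so it should stay supportive.

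The cost is a change of wording and a missing-data method to specify. The stated sample size need not be rewritten. The downside is that non-attendance dilutes the intention-to-treat estimate, so the power of 0.931 at 30 per arm applies only if the full 1.04 kg effect is retained and no woman is lost.
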